**Methods/Design:**

The study protocol will be a single-blind randomised controlled trial. Forty women diagnosed with fibromyalgia will be randomly assigned into 2 groups: Aquatic Therapy (*n* = 20) or Land-based Therapy (*n* = 20). Both interventions include 60-min therapy sessions, structured into 4 sections: Warm-up, Proprioceptive Exercises, Stretching and Relaxation. These sessions will be carried out 3 times a week for 3 months. Primary outcomes are balance (static and dynamic) and pain (intensity and threshold). Secondary outcomes include functional balance, quality of life, quality of sleep, fatigue, self-confidence in balance and physical ability. Outcome measures will be evaluated at baseline, at the end of the 3-month intervention period, and 6-weeks post-treatment. Statistical analysis will be carried out using the SPSS 21.0 program for Windows and a significance level of *p* ≤ 0.05 will be used for all tests.

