### Procedures

The assessments will take place at the Faculty of Physiotherapy of the University of A Coruña (Spain). Three assessment blocks will be established to carry out the measurements. A group of blinded trained assessors will be in charge of each block. In the first block, sociodemographic data (years since FM diagnosis, marital status, employment status, education level, smoking, number of falls in the last 6 months and medication) and anthropometric data (age, weight, height and body-mass index) will be registered. Pain intensity, fatigue, sleep quality, quality of life and self-confidence in balance will also be assessed. The second block will focus on measuring the pain threshold for the 18 tender points and functional independence in performing activities of daily life. Finally, the third block will assess physical ability and static/dynamic balance. Patients will be evaluated at three different moments: At baseline, immediately after the end of treatment and at 6-weeks follow-up.

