### Randomisation

Once the patients have read and signed the informed consent, those who have met the inclusion criteria, will be randomly assigned to one of the two intervention groups:Active Control Group: Land-based exercise program (CG *n* = 20).Experimental Group: Water exercise program (EG *n* = 20).

The randomisation will be carried out in a 1:1 manner via a computer-based scheme. The allocation will be concealed using sealed and opaque envelopes, numbered consecutively [18]. An independent researcher who will not participate in other study procedures will perform the randomisation process. The flow diagram of the study is summarised in Fig. 1.

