### Interventions

The interventions designed in this protocol consist of two similar physiotherapy protocols for people with FM. Both will include 60-min sessions that will be carried out 3 times a week for 3 months by a physiotherapist, in groups of 8–9 people maximum.

Both interventions will be based on: 15 min of warm-up, 25 min of proprioceptive exercises, 8 min of stretching and 12 min of relaxation.

For adequate training of balance and postural control, patients will be required to contract their local musculature (“core stability”) before starting any specific exercise. The transversus abdominis, pelvic floor muscles, internal oblique and multifidus form the local musculature. The most important aspect of achieving core stability will be co-activation of the first two muscles, for which patients will have to place their pelvis in a neutral position. Before starting the interventions, patients will receive anatomy and palpation classes to aid in identification of the involved musculature and how its contraction is perceived.

The protocols have been created by the main researcher based on available scientific evidence. The protocols were designed with the intention of being as similar as possible in order to attribute any statistically significant difference in outcomes between the two groups to the environment where the interventions were performed. Sessions will be pre-programmed with a progression in difficulty over the intervention period: Shorter pauses, higher exercise intensity, eyes closed, etc.

Patients will not be allowed to begin any other activity during the study period. They will have to report any problems, whether event-related or not, as well as any medication changes.

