### Statistical issues

#### Sample size calculation

The sample size was calculated to find a difference of ± 2.5 points between intervention groups on the VAS pain intensity scale [40], with a standard deviation of 2.5 points [41].

In order to achieve a statistical power of 80% with a significance level of *p* ≤ 0.05 and assuming a 20% dropout rate, an estimated 20 participants are required in each of the intervention groups. This sample size allows for detecting differences of 2 ± 2 s in the TUG test, with a statistical power of 80% and a significance level of *p* ≤ 0.05, assuming a 20% dropout rate.

The sample size was defined for a bilateral hypothesis and was carried out by the ENE software.

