## Discussion

The main objective of this randomised controlled trial is to determine the effectiveness of two physiotherapy protocols in improving balance and decreasing pain in women with FM, at the end of the intervention and at 6-weeks follow-up. With the study conclusion, we expect to test the following null hypothesis: “There is no difference in balance or pain for participants undergoing physiotherapy interventions on land or in water”. The balance disorder observed in FM is a sympton that has been discovered only recently. This is why there are very few publications regarding. Specifically, in the MEDLINE database, we were able to identify only 11 randomized controlled trials that included physical interventions and balance improvement was included in their objectives. Of these 11 clinical trials, only three included physiotherapy as a treatment method [43–45]. Given this, we expect the study conclusion to contribute to the fund of scientific knowledge, providing evidence that physiotherapy is a safe and effective tool in the management of FM symptoms, specifically balance disorders and pain.

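### The Discussion expects evidence that physiotherapy is safe, but no outcome or named analysis covers harm, and 20 women per arm cannot support that conclusion

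*Protocol article*

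**What the plan says.** **Expected conclusion.** In the Discussion, the authors expect the study to contribute by "providing evidence that physiotherapy is a safe and effective tool in the management of FM symptoms".

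**Outcomes.** The Abstract states: "Primary outcomes are balance (static and dynamic) and pain (intensity and threshold"), followed by "Secondary outcomes include functional balance, quality of life, quality of sleep, fatigue, self-confidence in balance and physical ability". The Outcome measures sections describe these same domains, and none is a harm. The Statistical analysis section names no summary or comparison of harms. The Sample size calculation rests on VAS pain, with a check on the Timed Up & Go.

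**Harm collection.** Under Interventions, the article says of the patients: "They will have to report any problems, whether event-related or not, as well as any medication changes". It gives no timing, list of events or recipient for these reports.

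**Nearest related item.** Under Procedures, the first assessment block records, among the sociodemographic data, "number of falls in the last 6 months and medication". Patients are evaluated at three times: "At baseline, immediately after the end of treatment and at 6-weeks follow-up".

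**The concern.** A conclusion about safety needs an outcome that measures harm, collection that works alike in both arms, and enough women for the result to exclude harm rates that matter. The article announces the conclusion and provides none of these three.

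The interventions cannot be masked from the women. One takes place in a sports-complex pool and the other in a faculty laboratory. The article describes the assessors as blinded, but does not route problem reports through them. What is reported may therefore depend on the arm for reasons other than risk.

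Harm is not far-fetched here. Eligibility requires a balance complaint of at least 5 on the questionnaire item. The exercises include jumps and work on unstable surfaces, and they progress to closed eyes. The exclusion of chlorine allergy, heat intolerance and water-related anxiety shows that pool-specific problems were considered.

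At stake is how a short list of problems would be read. It could mean low risk or low reporting, and the article gives no way to tell which.

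**Working it through.** **1. The plan's own sample size.** Inputs from the Sample size calculation: difference 2.5, SD 2.5, two-sided 0.05, power 80%, dropout 20%.

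- n per arm = 2 × (1.960 + 0.842)² × (2.5/2.5)² = 15.7, rounded up to 16.
- 16/0.8 = 20 per arm, as the article states.
- The Timed Up & Go inputs (difference 2, SD 2) give the same ratio and so the same 16 and 20.

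The figure reproduces. Harm played no part in it.

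**2. What an empty harm record would exclude if every event were captured.** The exact two-sided 95% upper limit for 0 events in n women is 1 − 0.025^(1/n).

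| Women | Upper limit |
|---|---|
| One arm, n = 20 | 16.8% |
| One arm, n = 16 (20 less 20% dropout) | 20.6% |
| Both arms pooled, n = 40 | 8.8% |

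The pooled figure says nothing about water against land.

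**3. What incomplete capture would do.** The documents give no capture rate, so a range is assumed. With true risk p = 10% and a share s of events reported, the chance of at least one report among 20 women is 1 − (1 − 0.10 × s)^20.

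| Share captured (assumed) | Formula | At least one report | Empty record |
|---|---|---|---|
| 100% | 1 − 0.900^20 | 88% | 12% |
| 75% | 1 − 0.925^20 | 79% | 21% |
| 50% | 1 − 0.950^20 | 64% | 36% |
| 25% | 1 − 0.975^20 | 40% | 60% |

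**4. Whether the falls item fills the gap.** The article lists it as sociodemographic data and does not call it an outcome. Suppose it were asked again at every visit. Treatment lasts 3 months and the last visit is 6 weeks later, so the later visits fall about 3 and 4.5 months after baseline. A 6-month look-back would reach about 6 − 3 = 3 months and 6 − 4.5 = 1.5 months before treatment. It would mix falls before and during the trial.

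**The case against.** **The article is condensed.** How harms are asked about, by whom and when may stand in the full protocol, which is not shown. This is right as far as it goes. A reader might infer that the trial has no other harm collection, and the article does not support that. It supports only that no other route is stated here. The point does not rest on missing operational detail. It rests on a conclusion announced in print that the printed outcomes, analysis and sample size do not serve.

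**Reports are not merely volunteered.** A reader might take the rule as voluntary. The wording obliges patients to report, covers any problem whatever its cause, and applies equally to both arms. It remains patient-initiated, by women who know their arm.

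**Some harm-related data exist.** Falls and medication appear in the first block. Weekly average pain, the impact questionnaire and fatigue are measured at all three evaluations, so sustained worsening would partly show. Flares between visits would be missed, and none of these is defined as a harm. A physiotherapist is present at every session, but the article does not say that events are recorded there.

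**The sentence is a hope, with no decision rule attached.** The main objective and null hypothesis concern only balance and pain, and no planned step turns an empty record into a safety finding. It would go too far to say that the trial will report safety from silence. What stands is that the article names this conclusion as expected.

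**The upper limits do not measure the collection rule.** This is correct. They follow from the number of women and would be the same under any collection method. Only the capture table concerns collection, and its shares are assumed.

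**Conclusion.** The point holds as a mismatch within the article: a safety conclusion is expected without a harm outcome, a named harm analysis or a sample that could support it.

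- **From the sample size alone.** A clean record in one arm is compatible with harm in about 1 woman in 6 (16.8%), or about 1 in 5 with 16 completers (20.6%). This assumes complete capture and is enough to show that safety cannot be concluded.
- **From the collection rule.** The loss depends on an unknown capture rate. For a true 10% risk, the chance of an empty record rises from 12% with full capture to between 21% and 60% over the assumed range of 75% down to 25%.

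A reader might also infer that reporting will differ between water and land. The design permits this, but nothing in the article shows that it will happen or in which direction.

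The efficacy analyses are not affected. The change is worth making before data collection, because events not asked about during the trial are hard to recover comparably later.

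**What to change.** 1. **Limit the claim.** In the Discussion, replace the expected statement of safety with a descriptive one: the number of women with each type of event per arm, with exact 95% intervals, and no claim beyond what those intervals exclude.

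2. **Ask every woman the same questions.** At the end-of-treatment and 6-week visits, give all women in both arms one short self-completed checklist: injury, fall since the last visit, symptom flare that caused a missed session, and event in or after a session. Include women who stopped the sessions where they can be reached.

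3. **Protect the blinding.** Have the checklist handed in after the blinded assessments and kept from the outcome assessors. The first block also collects the pain score, and an answer that mentions the pool would reveal the arm.

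**Cost.** A few minutes at two existing visits, one descriptive table and one changed sentence, with no new visits and no larger sample. The limitations are recall over up to 3 months, remaining reporting differences because the women know their arm, and a less favourable safety statement. The upper limits in the first table of the working do not shrink; the change makes the record more complete and more comparable.

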### Aquatic therapy

The twenty patients included in the EG will perform aquatic therapy in the Rialta Sports Complex, in A Coruña (Spain). The water temperature is 30 °C, with less than 1 °C of variation, and the environmental temperature is 27.5 °C, with less than 1 °C of variation. Sessions will be given in a swimming-pool of 20 × 6 m, with a 120-cm depth. The aquatic therapy protocol is described in Table 2.

**Table 2 Tab2:** Description of aquatic therapy protocol

Exercise blocks	Exercise descriptions	Repetitions/Action/Pause
Warm-up (15 min)	1. Running in water: With water at waist level, patients will run along the bottom of the pool, changing trajectory. 2. Can-Can kicks: Submerged to chest depth, patients will kick the water with alterating legs. 3. Hydro-Jumps: With feet on the pool’s floor, patients will jump, bending their knees at the highest point in their jump. 4. Pedaling: With a pool noodle under the neck, patients will move their legs in the motion of pedaling a bicycle while moving along the pool. 5. Rocking Horse: With one foot before the other, patients will alternate jumps with the front and back leg. 6. Relay Race: 2 groups. The winner will be the group that returns the baton to the first participant in the shortest time.	1. 3 min uninterrupted activity. 2. 3/30 s/15 s. 3. 3/30 s/15 s. 4. 3 min uninterrupted activity. 5. 3/30 s/15 s. 6. 2/1 min/20 s.
Proprioceptive exercises (25 min)	1. Playing Catch: In a group, patients will be sitting on a pool noddle and will have to maintain balance while throwing and catching the ball.	1. 3 min uninterrupted activity.
	2. Balance over pool noodles: Patients will be sitting on a pool noodle with hips and knees bent 90° and will have to keep balance in 3 different positions: a. With arms submerged and 90° abduction; b. one arm out of water and the other under water; c. from the initial position, they will have to do a trunk extension with shoulder extension, hip extension, knees pointing to the pool’s floor and neck extension.	2. 2 (for each position)/1 min/20 s.
	3. Turbulence standing: Standing, with water at the level of the chest and arms along the body; patients will have to do quick and short flexion/extension movements with the ULs generating significant turbulence. A good activation of local musculature will be essential for avoiding imbalance.	3. 4/15 s/15 s.
	4. Exercises with kickboard: a. Patients will be sitting on a kickboard, with water at the height of neck. They will have to keep afloat with only the aid of pedaling and without moving along the pool. b. With one foot on the kickboard and the other on the pool’s floor, patients will have to lower the kickboard and place it 10 cm above the pool’s floor. They will have to maintain this position and move the kickboard forward, backward and sideways without allowing it to go to the water’s surface. The exercise will be done with both LLs, first placing the kickboard vertically and then horizontally.	4. a. 2/1 min/20 s.; b. 2/40 s/15 s.
	5. Double pool noodle: Patients will be standing with a pool noodle in each hand. They will have to submerge them in the water while raising knees to chest.	5. 3/50 s/20 s.
	6. The boat: 2 groups. Patients will have to submerge a large mat while maintaining a standing position with different supports: Double, single-leg and tandem.	6. 3 min uninterrupted activity.
Stretching (8 min)	Gastrocnemius, quadriceps, ischiotibial, adductors, quadratus lumborum, deltoid, triceps brachii, superior trapezius.	2 (right and left side)/30 seg/5 seg.
Relaxation (12 min)	An Ai-Chi sequence with music. 6 movements of the 19 that comprise the Ai-Chi done in the following order: “Folding”, “Soothing”, “Gathering”, “Freeing”, “Shifting” and “Accepting”.	12 min uninterrupted activity.

*ULs* upper limbs, *LLs* lower limbs

### Land-based therapy

The twenty patients included in the CG will perform the intervention in one of the laboratories at the Faculty of Physical Therapy. The land-based therapy protocol is described in Table 3.

**Table 3 Tab3:** Description of land-based therapy protocol

Exercise blocks	Exercise descriptions	Repetitions/Action/Pause
Warm-up (15 min)	1. Vigorous Walking: Patients will have to walk forwards, backwards, snaking and changing direction energetically. 2. Standing exercises: a. On one leg, with an UL and its contralateral LL, patients will do a simultaneous abduction followed by addution. b. The shoulder flexion movement is combined with contralateral knee elevation. c. Patients will perform jumping jacks. 3. Ball Jumps: Patients will be sitting on a Bobath ball and will have to jump. 4. Pedaling: Patients will be positioned face up, with the hips and knees bent 90° and will have to do a pedaling motion with their legs, keeping the pelvis in a neutral position. 5. Relay Race: 2 groups. The winner will be the group that return the baton to the first participant in the shortest time.	1. 3 min of uninterrupted activity. 2. a. and b. 6 (3 for each diagonal)/15 s/5 s; c. 3/20 s/10 s. 3. 3/45 s/20 s. 4. 3/45 s/20 s. 5. 3/1 min/20 s.
Proprioceptive exercises (25 min)	1. Playing Catch: Patients will be placed in a circle and sitting on a Bobath ball. With single-foot support, they will have to maintain a good position while throwing and catching the ball.	1. 3 min of uninterrupted activity.
	2. The bridge: a. Patients will be positioned face up on a mat, with arms along the body and feet on a Bobath ball. They will have to raise their buttocks off the floor and hold this position (the bridge). b. Starting from the previous position, patients will do the bridge raising one of the LL supported on the ball together with the contralateral UL at the same time.	2. a. 2/1 min/20 s.; b. 4 (2 for each diagonal)/40 s/5 s.
	3. The knight: With one knee on a Dynair and the contralateral foot on a hedgehog (Erizo Senso® Balance), patients will have to maintain the position without losing balance.	3. 6 (3 for each side)/30 s/10 s.
	4. Standing balance: Standing on a Dynair, patients will have to maintain their balance while moving their center of gravity forward, backward and sideways. There can not be any contact with the floor through the Dynair. The exercise will also be performed on one leg.	4. 3/1 min/15 s.
	5. Superman: On all fours, with hands holding a roll (SISSEL® Pilates Roller), patients will have to perform and hold the superman position (simultaneous extension of an UL and contralateral LL). The exercise will also be performed dynamically: Hand touching the knee and then moving away, while keeping the pelvis in a neutral position.	5. 8 (4 for each diagonal: 2 dynamic and 2 keeping the position)/30 s/10 s.
	6. Exercises with the roll (SISSEL® Pilates Roller): a. Patients will be sitting on one of the roll’s ends and must move their trunk backward (reaching the stability limit), while keeping both feet fully supported on the floor. b. With the spine resting on the roll and hands and feet on the floor, patients will place their hips and knees in a flexion of 90°, without losing balance. This exercise will also be performed dynamically (raising and lowering the legs) and removing one of the hand supports.	6. a. 3/15 s/10 s.; b. 4 (2 dynamic y 2 keeping the position)/50 s/10 s.
Stretching (8 min)	Gastrocnemius, quadriceps, ischiotibial, adductors, quadratus lumborum, deltoid, triceps brachii, superior trapezius.	2 (right and left side)/30 s/5 s.
Relaxation (12 min)	Jacobson Progressive muscle relaxation, with classical music.	12 min of uninterrupted activity.

*UL* upper limb, *LL* lower limb, *Dynair* Balance Soft Disc

### Statistical issues

#### Sample size calculation

The sample size was calculated to find a difference of ± 2.5 points between intervention groups on the VAS pain intensity scale [40], with a standard deviation of 2.5 points [41].

In order to achieve a statistical power of 80% with a significance level of *p* ≤ 0.05 and assuming a 20% dropout rate, an estimated 20 participants are required in each of the intervention groups. This sample size allows for detecting differences of 2 ± 2 s in the TUG test, with a statistical power of 80% and a significance level of *p* ≤ 0.05, assuming a 20% dropout rate.

The sample size was defined for a bilateral hypothesis and was carried out by the ENE software.

### Statistical analysis

Analysis will be descriptive of all outcomes included in the study, expressing quantitative outcomes with their mean ± standard deviation and qualitative outcomes with their absolute value, percentage and 95% confidence intervals.

The association between qualitative outcomes will be studied using the Chi-square test. After checking normality with the Kolmogorov-Smirnov test, the Student *T* test or the Mann–Whitney *U* test will be used to perform mean comparison. The mean comparison between two or more categories will be studied with the ANOVA test or Kruskal-Wallis test, as appropriate.

The correlation between quantitative outcomes will be analysed with the Pearson or Spearman correlation coefficients, as appropriate.

The mean comparisons for related outcomes in two different moments will be studied with the Wilcoxon test. Friedman test will be used when comparing more than two moments. In addition, the clinical relevance of the intervention will be studied by calculating the relative risk, relative risk reduction, absolute risk reduction and the number needed to treat. All of these measures will be presented with their 95% confidence interval.

A multivariate analysis by multiple linear regression or logistic regression to adjust for the effectiveness of the intervention according to possible confounding factors and to determine what other outcomes might be associated with each result will be carried out. Only the outcomes that show a statistical significance p <0.20 in the bivariate analysis, will be included in the multivariate regression analysis. In addition, a stepwise backward modelling strategy will be carried out.

All analysis will be done by intention to treat [42], where the total value of randomisation is preserved and control of any counfounders’ effect is insured.

The significance level set for all the analysis will be *p* ≤0.05. The SPSS statistical software, version 21.0 (SPSS, Chicago, IL) will be used for all analysis.

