#### Dynamic balance

Timed Up & Go Test:

This test is a functional mobility test [20] whose purpose is to assess balance in the sitting position, transfers from a sitting position to a standing position and vice versa. It also evaluates stability during ambulation and direction changes while in gait without using compensatory strategies. The test consists of standing up from a chair with armrests and walking, at a normal speed, for 3 m, turning 180° and walking back to the chair. It will be practised once in order to insure that methodology is clear. At the time of assessment, only one single attempt will be registered. The test is measured in seconds and quantifies the time that the patient takes to complete the walk. A time of 10 s or less is considered normal and a time longer than 14 s is indicative of impaired balance and a high risk of falls [27].

Gait test:

The patient will have to walk, at a normal speed, for 8 m. The test will be practised once. As a limitation of optical range of the camera, only 3–4 gait cycles will be captured. Therefore, the 3 central meters of the walk should be used in the analysis of gait parameters.

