### Pain

#### Pain intensity

It will be measured with the EVA, a 10 cm long line with the value 0 on the left indicating “no pain” and the value 10 on the right indicating the “worst imaginable pain” [28]. The distance along the line indicated by the patient will correlate with their average pain intensity in the last week. Scores between 0 cm and 3 cm are classified as “mild pain”; between 4 cm and 7 cm “moderate pain” and between 8 cm and 10 cm “severe pain”.

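### Clinical relevance is to be judged by RR, ARR and NNT, although the trial is sized on mean differences in two continuous outcomes and the article designates no event

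*Protocol article*

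**What the plan says.** The Statistical analysis section states that "the clinical relevance of the intervention will be studied by calculating the relative risk, relative risk reduction, absolute risk reduction". The NNT completes the list, and an interval at the 95% level is promised for each measure. The section names no outcome, threshold or assessment time for these measures. For quantitative outcomes it promises means with standard deviations and a t-test or Mann-Whitney test. It also plans regression models adjusted for confounders. It promises no interval for a between-arm mean difference.

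The Sample size calculation section works on the continuous scale. It aims at "a difference of ± 2.5 points between intervention groups on the VAS pain intensity scale". The assumed SD is also 2.5 points. The section adds that the same number of women allows "detecting differences of 2 ± 2 s in the TUG test".

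Cut-offs are printed elsewhere as aids to reading the scales:
- Pain intensity has three severity bands, beginning with "Scores between 0 cm and 3 cm are classified as" mild.
- Dynamic balance gives two TUG limits: "A time of 10 s or less is considered normal and a time longer than 14 s" suggests impaired balance.
- Romberg's test has a positivity rule without a number.
- The Berg scale has a limit at 45, and the ABC scale has limits at 50, 67 and 80%.

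None is tied to the RR, ARR or NNT. There are two assessments after baseline: end of treatment and 6 weeks later.

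**The concern.** The article makes a positive choice of scale for clinical relevance, and that scale does not match the one the trial was built on. The 2.5-point and 2-s differences are the only statements of a worthwhile effect that are tied to the design, yet relevance is not read against them. A reader will instead get ratios and an NNT from a dichotomy in about 16 to 20 women per arm.

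Two things follow. First, with so few women the ARR interval will often include zero even when the planned effect is real. The NNT interval then passes through infinity and cannot be read in the usual way. Second, the same true effect gives very different NNTs at different printed cut-offs, so the stated verdict on relevance turns on a choice that this article leaves open.

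**Working it through.** **1. The plan's own figure.** Inputs from Sample size calculation: difference 2.5, SD 2.5 (VAS); difference 2, SD 2 (TUG); two-sided 0.05; power 80%; dropout 20%. Both effects equal 1 SD.

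n per arm = 2 × (1.96 + 0.84)² × (SD/difference)² = 15.7, rounded up to 16. Then 16 / 0.80 = 20. The stated 20 per group reproduces for both outcomes, so the sizing rests on mean differences. With 16 per arm the t-test has 78% power.

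**2. The same effect after dichotomising.** Assume normal outcomes with a 1-SD shift, lower values better, and a responder defined as a woman at or below the cut-off. Write c for the cut-off in SDs from the mean of the better arm. Then p(better) = Φ(c), p(other) = Φ(c − 1), ARR = p(better) − p(other) and NNT = 1/ARR. The Wald interval is ARR ± 1.96 × √[p₁(1 − p₁)/n + p₂(1 − p₂)/n] on the observed proportions. I summed over all possible pairs of binomial counts to get the chance that it includes zero.

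| c | p(other) | p(better) | ARR | NNT | Includes zero, n = 16 | Includes zero, n = 20 |
|---|---|---|---|---|---|---|
| −0.5 | 0.067 | 0.309 | 0.242 | 4.1 | 56% | 43% |
| 0 | 0.159 | 0.500 | 0.341 | 2.9 | 38% | 29% |
| 0.5 | 0.309 | 0.691 | 0.383 | 2.6 | 38% | 23% |
| 1 | 0.500 | 0.841 | 0.341 | 2.9 | 38% | 29% |
| 1.5 | 0.691 | 0.933 | 0.242 | 4.1 | 56% | 43% |

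Take the most favourable cut-off (c = 0.5) at its expected values with n = 16. The standard error is √(2 × 0.309 × 0.691/16) = 0.163, so the half-width is 0.320 and the ARR interval is 0.063 to 0.703. That is an NNT of 1.4 to 16.

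**3. The mean difference on the same data.** With n = 16 the 95% half-width is t(30 df) × SD × √(2/16). For VAS this is 2.042 × 2.5 × 0.354 = 1.8 points. For TUG it is 2.042 × 2 × 0.354 = 1.4 s. At the planned effects the intervals are about 0.7 to 4.3 points and 0.6 to 3.4 s. Both exclude zero and can be read directly against 2.5 points and 2 s.

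**4. Dependence on the printed cut-off.** The article gives no control means, so these are assumptions, shown over a range. Example: TUG control mean 11 s, other arm 9 s, SD 2 s.
- At 10 s: Φ(0.5) − Φ(−0.5) = 0.691 − 0.309 = 0.383, NNT 2.6.
- At 14 s: Φ(2.5) − Φ(1.5) = 0.994 − 0.933 = 0.061, NNT 16.5.

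| Outcome | Assumed control mean | NNT at lower cut-off | NNT at upper cut-off |
|---|---|---|---|
| TUG (10 s, 14 s) | 10 s | 2.9 | 47 |
| | 11 s | 2.6 | 16.5 |
| | 12 s | 2.9 | 7.4 |
| | 13 s | 4.1 | 4.1 |
| VAS (3 cm, 7 cm) | 5 | 2.7 | 5.7 |
| | 6 | 3.3 | 3.8 |
| | 7 | 4.6 | 2.9 |

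**The case against.** The strongest reply has four parts.

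- **The article condenses a fuller plan.** An event definition is the sort of detail that a full protocol or SAP would hold. This stands: the missing definition alone would be no finding. What remains is the scale that the article itself chooses for relevance.
- **The responder measures are an addition.** The between-arm test stays on the continuous scale, so the power that the trial was sized for is not lost. This stands in full. Reporting an NNT beside a mean difference is also ordinary practice, but here no mean difference with an interval is promised beside it.
- **Usable cut-offs are printed.** It would be wrong to say that no event could be formed. The VAS bands leave 3-4 cm and 7-8 cm unassigned, but a single boundary such as 3 cm or less still gives a complete binary outcome. What is lacking is the designation of one.
- **Intention to treat implies 20 per arm, not 16.** With 20 analysed and the same 1-SD separation, the ARR interval would include zero in about 23-43% of trials. Counting women without data as non-responders would dilute the separation somewhat. The problem shrinks but remains.

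A reader might infer that the cut-off will be picked after the data are seen and that false positives will be inflated. The article does not say so. It attaches intervals, not a significance test, to these measures, so a type I error rate for a best-of-several chi-square test would describe something that the plan does not specify.

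**Conclusion.** The point holds as a mismatch of scale. Relevance is to be judged on binary measures for which the article designates no event, while the trial is sized on mean differences of 1 SD in two continuous outcomes. With 16 completers per arm the ARR interval would include zero, and the NNT interval be unbounded, in roughly 38-56% of trials in which the planned effect is real. The NNT can differ several-fold between printed cut-offs, although for some assumed control means it barely differs.

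The figures assume normal outcomes, a Wald interval and cut-offs between −0.5 and 1.5 SD from the better arm's mean; cut-offs further out do worse. The NNT examples rest on assumed control means. The sample size, the main test and its power are not called into question. This is a cheap improvement in how the result is read, not a flaw that undermines the trial.

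**What to change.** In Statistical analysis, state that clinical relevance is judged mainly by the between-arm mean difference with its 95% confidence interval at end of treatment, read against the 2.5-point VAS and 2-s TUG differences in Sample size calculation.

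If RR, RRR, ARR and NNT are kept, label them supplementary. Name one outcome, one cut-off and one time point before unblinding, and say how women without a value are counted. Report the risk difference with its 95% interval first, so that a reader can see whether the NNT interval is bounded.

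The cost is a few sentences, with no new data or participants. The downside is small: the responder measures become secondary, and any single cut-off is somewhat arbitrary.
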